#### Validation of the A/P CT decision instruments

The validation phase of the study will involve the collection of the combination of clinical variables forming the A/P CT decision instruments [17]. A case will be considered true-positive if the patient has at least one of the variables and is given a diagnosis of SAPI based on the designated imaging modality. Cases of patients given a diagnosis of SAPI but in whom none of the variables are present will be classified as false-negative cases. Cases of patients with none of the variables and no SAPI will be classified as true-negative cases. The remaining cases will be classified as false-positive cases. These values will be used to calculate point measures and 95 percent confidence intervals (CIs) for sensitivity, NPV and specificity of the decision instruments.

We will consider an instrument to be adequately validated if the lower confidence intervals for sensitivity and negative predictive value exceed 98%.

### Preliminary work

In this section we describe the development of our candidate criteria, our primary and secondary outcomes, and our sample size calculations.

### Assessing the inter-rater variability of criteria used in evaluating patients with blunt trauma for significant abdominal-pelvic injuries

#### Purpose

To determine the inter-rater variability of candidate criteria used to evaluate patients with blunt trauma for evidence of abdominal-pelvic injuries.

#### Methods

Physicians performed paired evaluations of patients with blunt trauma undergoing A/P CT imaging. Each physician independently determined whether each patient had any of the following characteristics: 1) abdominal pain or tenderness, 2) flank pain or tenderness, 3) pelvic pain or tenderness, 4) hip or iliac pain or tenderness, 5) midline lumbar spine or sacral pain, 6) abdominal distention, 7) abdominal or pelvic bruising, 8) abdominal or pelvic abrasion, 9) evidence of genital-urinary trauma, 10) abnormal alertness, 11) evidence of intoxication, 12) distracting painful injury, 13) hypotension, 14) tachycardia, 15) unstable vital signs, 16) low hemoglobin or hematocrit, 17) falling hemoglobin or hematocrit, 18) dangerous mechanism of injury, 19) abnormal plain radiography. Responses were compared using the Scott’s pi statistic, with a point measure of 0.40 or greater interpreted to represent substantial inter-rater agreement.

#### Results

The physicians exhibited substantial inter-rater agreement for the following criteria: abdominal pain or tenderness (π = 0.64), flank pain or tenderness (π = 0.43), pelvic pain or tenderness (π = 0.41), hip or iliac pain or tenderness (π = 0.49), midline lumbar spine or sacral pain (π = 0.47), abnormal alertness (π = 0.48), evidence of intoxication (π = 0.68), distracting painful injury (π = 0.43), and hypotension (π = 0.63).

The physicians exhibited moderate or poor inter-rater agreement (π < 0.40) for abdominal distention, and abdominal or pelvic bruising or abrasion, tachycardia, unstable vital signs, and low or falling hemoglobin or hematocrit. The clinicians also exhibited poor inter-rater agreement on evidence of genital-urinary trauma (π = 0.23), but the exclusion of this criterion is mitigated by the fact that there were no patients who sustained significant genital-urinary trauma among our inter-rater assessment cohort.

#### Conclusions

We found substantial agreement between clinicians in their assessments of abdominal pain or tenderness, flank pain or tenderness, pelvic pain or tenderness, hip or iliac pain or tenderness, midline lumbar spine or sacral pain, abnormal alertness, evidence of intoxication, distracting painful injury, and hypotension. We were unable to obtain a meaningful assessment of genital urinary trauma due to its rarity among our cohort, and we found only moderate to poor agreement on the presence or absence of all other criteria.

### Defining significant injuries of the abdomen and pelvis

#### Purpose

To obtain consensus definitions of the significant injuries of the abdomen and pelvis that can serve in defining our primary and secondary outcome measures.

#### Methods

We employed a modified Delphi process involving a representative from emergency medicine, trauma surgery and trauma radiology from each of the three core centers. We provided each representative an initial list of individual abdominal and pelvic injuries. Participants were then asked to rate each injury as “clinically major,” “clinically minor,” or “clinically insignificant,” and to provide any comments, questions or clarifications they deemed appropriate. Responses to the initial list of injuries were then tabulated, and the tabulated results, along with the respondent comments, were sent back to the respondents for further review. We then provided reviewers with a final list of the individual abdominal and pelvic injuries, and asked them to provide a final classification based on their review of the tabulated results and reviewer comments. We based our final classification of the significance of each injury on the majority outcome ranking for each injury. Any injury patterns associated with tie votes were automatically assigned to the higher injury severity category.

#### Results

The respondents assigned “clinically major” importance to all injuries requiring intervention, including injuries to the bladder or ureter, bowel, diaphragm, genitals, hepatobiliary structures, hip, pancreas, pelvis, renal system, retroperitoneum, spine, spleen, and vasculature, including aorta, iliac or other vessels. Injuries to the spine that resulted in instability or neurological compromise were considered clinically major, even if they did not require intervention, as were injuries to the aorta. Respondents assigned “clinically minor” status to injuries that required observation but not intervention for the following areas: bladder or ureter, bowel, diaphragm, genitals, hepatobiliary structures, hip, pancreas, pelvis, renal system, retroperitoneum, spine (stable with no neurological compromise), spleen, and vascular injuries that do involve the aorta. Injuries that did not require intervention or observation were classified as “insignificant,” with the exception of injuries to the aorta, and injuries to the spine that involve instability or neurological compromise.

#### Conclusions

Injuries of major clinical significance consist of all abdominal and pelvic injuries requiring intervention, as well as any injury to the aorta, and any injury to the spine associated with instability or neurological compromise. Injuries that require only observation, but no intervention, were considered clinically minor, provided they did not involve the aorta or spine, while injuries that required neither intervention nor observation were considered insignificant.

### Sample size calculations for derivation and verification studies

To be clinically reliable, the combined selective criteria must satisfy two requirements. First, patients identified as risk free by the decision instrument must never harbor injuries of major clinical significance. This is equivalent to requiring the instrument to have a 100% negative predictive value. Second, every patient with blunt trauma with an injury of major clinical significance must exhibit at least one of the risk criteria. This requirement implies that the sensitivity of decision instrument be 100%.

Verifying negative predictive value and sensitivity at an absolute level is not statistically possible with a finite sample size. However, it is possible to estimate limits for the true values of these proportions using exact statistical relationships. The lower confidence limit of a proportion (such as negative predictive value or sensitivity) is related to the total size of the study population. The quantitative relationship is expressed by the following equation from Fleiss [47]:

$$P_{L}=\frac{X}{X+(N‐X+1)\cdot F_{\frac{\alpha }{2},v_{1},v_{2}}}$$

Where:

P_L_ = Lower confidence limit for the proportion being studied (i.e. the lower confidence limit for the negative predictive value or sensitivity of selective criteria).

X = Number of times the event of interest is observed.

N = Total number of observations.

α = Statistical confidence value (Set to 0.05).

ν_1_ = Degrees of freedom for the numerator; ν_1_ = 2 [N—X + 1]

ν_2_ = Degrees of freedom for the denominator; ν_2_ = 2 X

F_α/2,ν1,ν2_ = One tailed value of the F-distribution with ν_1_ and ν_2_ degrees of freedom.

Validating a given P_L_ to a 95% level of statistical certainty implies that α = 5% (or α = 0.05). The main hypothesis of this study states that selective criteria will detect all injuries of major clinical significance in patients with blunt trauma without missing any such injuries. Thus, for purposes of sample size calculations, for either negative predictive value or sensitivity, the event of interest (presence of one of the risk criteria) should occur with every observation. Hence, X = N.

The degrees of freedom for the numerator and denominator are then given by:

ν_1_ = Degrees of freedom for the numerator; ν_1_ = 2 [N—X + 1] = 2 [N—N + 1] = 2

ν_2_ = Degrees of freedom for the denominator; ν_2_ = 2 X = 2 N

The expression for the lower confidence limit then becomes:

$$P_{L}=\frac{N}{N+(N‐N+1)\cdot F_{0.025,2,2N}}=\frac{N}{N+F_{0.025,2,2N}}$$

Practical concerns regarding radiographic charges and radiation health effects suggest that selective criteria will still remain cost effective and reduce mortality and morbidity even when missing 2 out of every 100 injuries. This implies that negative predictive value need only be verified to a 98.0% lower confidence level, or equivalently, P_L_ = 0.98. Substituting this value in the lower confidence limit equation yields an algebraic equation for our injury population size, with a solution of N = 317. Thus, to confirm that the decision instrument has a negative predictive value of at least 98.0%, the study must enroll 317 blunt trauma patients who have none of the risk criteria, and none of whom have injuries of major clinical significance. Since approximately 10% of victims of blunt trauma are free of the risk criteria, this derivation would require a population of 3,170 patients with blunt trauma. Unfortunately, confirming that the instrument has 98.0% sensitivity requires studying 317 patients having injuries of major clinical significance. Major injuries occur in only 5% of cases of blunt trauma, which implies that this study will need to prospectively evaluate 6,340 patients with blunt trauma. Consequently, study size is driven by the requirements of sensitivity. Both the derivation and validation phases of the study will need enroll sufficient patient to satisfy the sensitivity requirement, thus the entire study will need to enroll a total of 12,680 patients with blunt trauma.

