## Abstract

Although computed tomography (CT) of the abdomen and pelvis (A/P) can provide crucial information for managing blunt trauma patients, liberal and indiscriminant imaging is expensive, can delay critical interventions, and unnecessarily exposes patients to ionizing radiation. Currently no definitive recommendations exist detailing which adult blunt trauma patients should receive A/P CT imaging and which patients may safely forego CT. Considerable benefit could be realized by identifying clinical criteria that reliably classify the risk of abdominal and pelvic injuries in blunt trauma patients. Patients identified as “very low risk” by such criteria would be free of significant injury, receive no benefit from imaging and therefore could be safely spared the expense and radiation exposure associated with A/P CT. The goal of this two-phase nationwide multicenter observational study is to derive and validate the use of clinical criteria to stratify the risk of injuries to the abdomen and pelvis among adult blunt trauma patients. We estimate that nation-wide implementation of a rigorously developed decision instrument could safely reduce CT imaging of adult blunt trauma patients by more than 20%, and reduce annual radiographic charges by $180 million, while simultaneously expediting trauma care and decreasing radiation exposure with its attendant risk of radiation-induced malignancy. Prior to enrollment we convened an expert panel of trauma surgeons, radiologists and emergency medicine physicians to develop a consensus definition for clinically significant abdominal and pelvic injury. In the first derivation phase of the study, we will document the presence or absence of preselected candidate criteria, as well as the presence or absence of significant abdominal or pelvic injuries in a cohort of blunt trauma victims. Using recursive partitioning, we will examine combinations of these criteria to identify an optimal “very low risk” subset that identifies injuries with a sensitivity exceeding 98%, excludes injury with a negative predictive value (NPV) greater than 98%, and retains the highest possible specificity and potential to decrease imaging. In Phase 2 of the study we will validate the performance of a decision rule based on these criteria among a new cohort of patients to ensure that the criteria retain high sensitivity, NPV and optimal specificity. Validating the sensitivity of the decision instrument with high statistical precision requires evaluations on 317 blunt trauma patients who have significant abdominal-pelvic injuries, which will in turn require evaluations on approximately 6,340 blunt trauma patients. We will estimate potential reductions in CT imaging by counting the number of abdominal-pelvic CT scans performed on “very low risk” patients. Reductions in charges and radiation exposure will be determined by respectively summing radiographic charges and lifetime decreases in radiation morbidity and mortality for all “very low risk” cases.

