### Sample targets

Sensitivity = 95%; n = 125; N = 2,500; Total enrolled = 5,000

Sensitivity = 96%; n = 157; N = 3,140; Total enrolled = 6,280

Sensitivity = 97%; n = 211; N = 4,220; Total enrolled = 8,440

Sensitivity = 98%; n = 317; N = 6,340; Total enrolled = 12,680

Sensitivity = 99%; n = 637; N = 12,740; Total enrolled = 25,840

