### Sample size calculations for the assessment of work-up bias

For our assessment of work-up bias we need to verify that occult injuries among patients who are not selected for A/P CT imaging is negligible, as evidenced by a prevalence below 1.0%. The equations of Fleiss again provide the quantitative relationships needed to determine the sample size for the work-up bias study, and confirm this low prevalence [47]. The equations indicate that a sample of 368 un-imaged patients will be needed to confirm that the prevalence of occult injuries does not exceed 1.0%. Thus our work-up bias assessment will need to enroll and follow 368 patients with blunt trauma who do not undergo CT imaging on their initial presentation.

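### The target of 317 injured patients does not solve the protocol's own sample size equation, which gives 183; the targets table and the work-up bias section disagree on a 99% bound (637 against 368)

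*Protocol article*

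**What the plan says.** The section on sample size for the derivation and verification studies gives an exact (F-distribution) lower limit for a proportion. Its inputs are explicit:

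- **Alpha:** "α = Statistical confidence value (Set to 0.05", tied to 95% certainty.
- **Tail:** "F_α/2,ν1,ν2_ = One tailed value of the F-distribution with ν_1_ and ν_2_ degrees of freedom". The reduced formula is printed with the value 0.025 filled in.
- **Misses:** none, since "the event of interest (presence of one of the risk criteria) should occur with every observation. Hence, X = N".
- **Target limit:** P_L = 0.98.

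The article says that substituting these "yields an algebraic equation for our injury population size, with a solution of N = 317". It divides 317 by a 5% prevalence of major injury to get 6,340 patients, and doubles that to 12,680 for the two phases. For negative predictive value it divides 317 by 10% to get 3,170. The Abstract repeats that validating sensitivity "requires evaluations on 317 blunt trauma patients who have significant abdominal-pelvic injuries".

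The Sample targets list gives 125, 157, 211, 317 and 637 injured patients for 95% to 99%. Its last row reads "Sensitivity = 99%; n = 637; N = 12,740; Total enrolled = 25,840". The work-up bias section, citing the same equations, says that "a sample of 368 un-imaged patients will be needed to confirm that the prevalence of occult injuries does not exceed 1.0" percent.

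Under Validation of the A/P CT decision instruments, success requires the lower 95% confidence limits for both sensitivity and negative predictive value to be above 98%.

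**The concern.** The equation, tail area, target and solution are printed together, so the result can be tested without any further document, and it fails. Two sections that rely on the same equations also give different answers to what is, with zero events, the same question.

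The figure matters because 317 fixes the size of both phases. It is presented as the number needed with no misses at 95% confidence. A reader would conclude that a single missed injury among 317 defeats validation. Under the article's own success rule, one miss still passes. The stated link between study size, confidence level and success rule is therefore wrong and should be settled before validation data are read.

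**Working it through.** **Inputs (all from the article):** alpha = 0.05, upper tail 0.025, X = N, P_L = 0.98, prevalence of major injury 5%, share of patients free of all criteria 10%.

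**1. Attempt to reproduce 317.** The printed formula is P_L = N / (N + F), with F the upper 0.025 point on 2 and 2N degrees of freedom. With no misses this equals 0.025^(1/N).

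- For P_L = 0.98 at N = 317, F would have to be 317 × 0.02 / 0.98 = 6.47.
- The actual value of F(0.025; 2, 634) is 3.71.
- So P_L = 317 / (317 + 3.71) = 0.9884, not 0.98.

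**2. Solve the equation.** N = ln(0.025) / ln(0.98) = 3.6889 / 0.020203 = 182.6, rounded up to 183. The limit at 183 is 0.98004.

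**3. The whole table.** The smallest N with 0.025^(1/N) at or above the target, against the stated n:

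| Lower limit | Formula | Stated | Ratio |
|---|---|---|---|
| 95% | 72 | 125 | 1.74 |
| 96% | 91 | 157 | 1.73 |
| 97% | 122 | 211 | 1.73 |
| 98% | 183 | 317 | 1.73 |
| 99% | 368 | 637 | 1.73 |

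**4. The work-up bias figure.** Zero events with an upper limit of 1% is the same calculation as a 99% lower limit: ln(0.025) / ln(0.99) = 367.04, rounded up to 368. That section is right at alpha 0.05, and the 637 in the table contradicts it.

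**5. Patients that follow from 183.** 183 / 0.05 = 3,660 per phase (stated 6,340). 2 × 3,660 = 7,320 in total (stated 12,680). For negative predictive value, 183 / 0.10 = 1,830 (stated 3,170).

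**6. What 317 delivers under the success rule (tail 0.025).**

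| Injured patients | Misses | Lower limit | Above 98%? |
|---|---|---|---|
| 317 | 0 | 98.84% | yes |
| 317 | 1 | 98.26% | yes |
| 317 | 2 | 97.74% | no |
| 183 | 0 | 98.004% | yes |
| 183 | 1 | 96.99% | no |

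The minimum sizes are 183 for no miss, 277 for one and 359 for two. So 317 lies in the range 277 to 358, where one miss is allowed.

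**7. Other routes to the stated figures.** None uses the stated inputs.

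- One-sided 0.05 with no miss gives 149 at 98%; a Wilson limit gives about 189.
- A tail between about 0.001658 and 0.001667 with no miss matches all five rows exactly.
- A tail of 0.0125 with one miss gives 125, 157, 210, 317 and 636.
- One-sided 0.05 with two misses gives 124, 156, 208, 313 and 628.

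**8. Chance of meeting the sensitivity criterion.** The true sensitivities are assumptions, not figures from the article. The injured count is taken as exactly 317 or 183, and the condition on negative predictive value is left out. For 183 the chance is s^183; for 317 it is s^317 + 317(1 − s)s^316.

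| Assumed sensitivity s | 183, no miss | 317, at most one miss |
|---|---|---|
| 99.0% | 16% | 17% |
| 99.5% | 40% | 53% |
| 99.8% | 69% | 87% |

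**9. Separate slip.** In the 99% row, 2 × 12,740 = 25,480, not 25,840.

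**The case against.** The strongest reply is that nothing in the results would be wrong. The stated size exceeds what the formula requires, the study is observational, and validation is judged on the observed lower limits, into which 317 does not enter. This stands, and it limits the severity. A reader might infer from a failed derivation that the study is underpowered or its success rule invalid; the figures show neither.

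A second reply is that the article need not tabulate how many misses are tolerated, because that follows from the success rule for any realised count. This also stands. The fault is the false solution, not a missing table.

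Three further readings are tempting but unsupported:

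- **A hidden multiplicity correction.** A tail near 1/600 matches all five rows, which invites the idea of an adjusted alpha of about 0.0033. The article mentions no such adjustment, and a tail of 0.0125 with one miss gives 317 exactly and every other row to within one. The source cannot be determined.
- **317 as the one-miss size.** It allows one miss, but the minimum for that is 277.
- **Enrolment should fall to 183 injured patients.** That would leave no room for a miss and, under the assumptions in the working, lower the chance of meeting the sensitivity criterion.

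**Conclusion.** The point holds as an error of derivation and an internal contradiction; it should be fixed. At the stated alpha, tail, zero misses and 98% target, the solution is 183, not 317. Every row of the targets table is overstated by about 73%, and 637 conflicts with the 368 obtained from the same equations. This rests only on inputs printed in the article; the conversion to 3,660 and 1,830 patients also uses its 5% and 10% figures.

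The direction is conservative: the study is oversized against its stated criterion. Keeping the larger target is defensible, because it allows one missed injury where 183 allows none. What cannot stand is presenting 317 as the zero-miss solution at 95% confidence. The mistaken total of 25,840 is minor and sits in a row that the study does not use.

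**What to change.** 1. In the sample size section, give 183 as the zero-miss minimum at 95% confidence: 3,660 patients per phase at 5% prevalence, and 1,830 for negative predictive value at 10%.
2. Correct the injured counts in Sample targets to 72, 91, 122, 183 and 368, with patients and totals following by division by 0.05 and doubling. If the existing last row is kept for any reason, its total should be 25,480.
3. Keep 317 and 6,340 per phase (12,680 in total) as a deliberate margin, and align the Abstract's wording. Suggested text: at 95% confidence, 317 injured patients allow one missed injury (lower limit 98.26%) but not two (97.74%); the minimum sizes are 277 for one miss and 359 for two.
4. If a stricter alpha was intended, state it with its reason and apply it to the validation limits as well.
5. If chances of success are quoted, label them as resting on assumed true sensitivities, a fixed count of 317 injured patients, and sensitivity alone.

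The cost is protocol wording. No patients, procedures or data items change.

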### Sample targets

Sensitivity = 95%; n = 125; N = 2,500; Total enrolled = 5,000

Sensitivity = 96%; n = 157; N = 3,140; Total enrolled = 6,280

Sensitivity = 97%; n = 211; N = 4,220; Total enrolled = 8,440

Sensitivity = 98%; n = 317; N = 6,340; Total enrolled = 12,680

Sensitivity = 99%; n = 637; N = 12,740; Total enrolled = 25,840

### Sample size calculations for the assessment of work-up bias

For our assessment of work-up bias we need to verify that occult injuries among patients who are not selected for A/P CT imaging is negligible, as evidenced by a prevalence below 1.0%. The equations of Fleiss again provide the quantitative relationships needed to determine the sample size for the work-up bias study, and confirm this low prevalence [47]. The equations indicate that a sample of 368 un-imaged patients will be needed to confirm that the prevalence of occult injuries does not exceed 1.0%. Thus our work-up bias assessment will need to enroll and follow 368 patients with blunt trauma who do not undergo CT imaging on their initial presentation.

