### Study sites and subjects

This prospective cohort study will be conducted at four Level 1 Trauma Centers, with wide variations in geographic location and patient populations. Including institutions from different environments (urban suburban, rural) enables us to increase the external validity of the instrument and is also necessary to assemble the large cohort of patients needed to obtain high levels of precision, small confidence intervals, and robust measures of sensitivity and negative predictive value that are needed to justify clinical application [8, 9, 11, 12, 16–21, 39, 40].

We will enroll patients using a prospective convenience sample of consecutive patients presenting to the ED between 0700–2300 (the times during which research assistants will be available). We will review ED logs and identify patients who are not enrolled, and we will compare the age, sex and injury severity scores of the enrolled and un-enrolled populations. We will adhere to the Standards for the Reporting of Diagnostic accuracy studies (STARD) guidelines for diagnostic accuracy studies and include a STARD flow diagram [41].

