### Work-up bias assessment

In concordance with prior NEXUS instruments, including the NEXUS C-spine, Head CT, and Chest CT rules [30, 33, 35, 46], our A/P decision tool is intended to be applied only to patients who are felt to have sufficient risk of SAPI to merit imaging. The tool is not intended for application on all patients with blunt trauma, particularly those who are determined, on the basis of clinical judgment, to have minimal risk of abdominopelvic injury and for whom A/P CT imaging is not ordered. Restricting application of the tool among low risk patients decreases the potential for generating false positive assessments, which could increase the rate of unnecessary imaging among low risk patients and markedly decrease the utility of the tool.

The success of this approach hinges on the reliability of clinical judgment, and requires that clinicians exhibit high sensitivity in their imaging decisions. High sensitivity for clinical judgment implies that clinicians will obtain imaging for virtually all injured patients, and that missed and occult injuries are rare. Therefore, an important component of our methodology is to assess the potential for unrecognized injuries among patients with blunt trauma and verify that unrecognized and occult injuries truly are rare.

Validating this approach, and verifying the high sensitivity of clinical judgment, is equivalent to assessing the potential for work-up bias, and requires a specific focus on assessing the prevalence of SAPI among patients with blunt trauma who do not undergo A/P CT imaging during their initial ED evaluation.

To conduct this assessment, we will have research assistants, present in the ED on a continuous basis, identify eligible patients during their initial visit and include them in our work-up bias study. We will complete criteria assessments for each patient at the time of presentation and follow each patient for a period of three months to determine whether at any time during this interval they returned for further care or evaluation or sought care at another facility after their discharge, whether they received any x-rays or imaging studies, and if so, what type, and whether they received any treatments, hospital admission, surgery, radiographic intervention, or died as a result of the injury.

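### An occult-injury prevalence below 1.0% in un-imaged patients does not verify that clinicians' imaging decisions are highly sensitive

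*Protocol article*

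**What the plan says.** The section Work-up bias assessment says the approach "requires that clinicians exhibit high sensitivity in their imaging decisions" and explains this as imaging almost everyone who is injured. It then states that "verifying the high sensitivity of clinical judgment, is equivalent to assessing the potential for work-up bias", and that this calls for measuring the prevalence of significant abdominal-pelvic injury (SAPI) in patients without initial CT.

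The same section sorts followed-up patients into three categories: (1) no missed or occult injury; (2) missed injury with at least one decision criterion present; (3) occult injury, with no criterion present. All three prevalences are to be reported with 95% confidence intervals, but only category 3 is used to judge work-up bias.

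Sample size calculations for the assessment of work-up bias sets the target: the study must show that "occult injuries among patients who are not selected for A/P CT imaging is negligible, as evidenced by a prevalence below 1.0"%. It concludes that "a sample of 368 un-imaged patients will be needed to confirm that the prevalence of occult injuries does not exceed 1.0"%.

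For the decision rule, Sample size calculations for derivation and verification studies says that "Major injuries occur in only 5% of cases of blunt trauma" and applies this figure to the imaged enrolment. It accepts two missed injuries per hundred as tolerable.

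**The concern.** Injury prevalence among un-imaged patients is 1 − NPV of the decision to image. Sensitivity is the share of all injured patients who were imaged. To get from one to the other, one needs the number of un-imaged patients and the number of injured patients among those imaged. The plan keeps the two measures apart for the rule, where it derives 3,170 patients for NPV and 6,340 for sensitivity. For the clinician's decision it treats them as one.

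The study could therefore meet its criterion and report that clinical judgment is highly sensitive, although the result does not establish this. The design rests on that assumption, and the article itself says under General design that it needs to be verified.

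**Working it through.** **Inputs**
- Criterion: prevalence below 1.0%, N = 368 (Sample size calculations for the assessment of work-up bias).
- "α = Statistical confidence value (Set to 0.05"), used as α/2 = 0.025; sized for no misses, since the event "should occur with every observation. Hence, X = N" (Sample size calculations for derivation and verification studies).
- Major-injury prevalence 5% and tolerated miss rate 2% (same section).
- Un-imaged:imaged ratio r, or un-imaged share u of all blunt trauma: not given, so assumed over a range.

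**The plan's own figure.** With zero events the exact upper limit is 1 − 0.025^(1/N). Setting it to 0.01 gives N = ln(0.025)/ln(0.99) = 367.04, so 368. At N = 368 the limit is 0.997%. The stated sample size reproduces.

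**Reading A: 5% injured among imaged patients** (as the figure is applied to enrolment). At a missed prevalence of 1.0%,

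share of injured left un-imaged = 0.01r / (0.01r + 0.05)

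| r | share left un-imaged | clinician sensitivity |
|---|---|---|
| 0.1 | 2.0% | 98.0% |
| 0.25 | 4.8% | 95.2% |
| 0.5 | 9.1% | 90.9% |
| 1 | 16.7% | 83.3% |
| 2 | 28.6% | 71.4% |
| 3 | 37.5% | 62.5% |

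Using the achieved limit of 0.997% changes little (16.6% at r = 1). With 10% injured among imaged patients, the share at r = 1 is 0.01/0.11 = 9.1%.

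**Reading B: 5% injured among all blunt trauma** (as the sentence is worded).

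share of injured left un-imaged = 0.01u / 0.05

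This gives 2% at u = 0.1, 5% at 0.25, 10% at 0.5 and 15% at 0.75. Because u is below 1, it is always below 20%.

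**Where the criterion would match the 2% tolerance.** Reading A: r = 0.05 × (0.02/0.98)/0.01 = 0.102. Reading B: u = 0.02 × 0.05/0.01 = 0.10. In both cases un-imaged patients must be few.

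**Prevalence needed for a 2% missed share.** Reading A, r = 1: 0.05 × (0.02/0.98) = 0.10%, which needs 3,614 patients with zero events. Reading B, u = 0.5: 0.02 × 0.05/0.5 = 0.20%, which needs 1,843.

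**Which injuries the bound covers.** The figures above generously apply 1.0% to every missed injury. The criterion is worded for occult injuries, which are category 3 only. A patient in category 2 was also injured and not imaged, so is equally a clinician miss, yet has no limit set. Meeting the criterion does not cap total missed injuries even at 1.0%.

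**The case against.** Several counter-arguments stand in part.

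- **The size depends on an assumption.** A reader might infer from the 5% figure that at least 1 in 6 injured patients could go un-imaged. The document does not support that. The figure needs a 1:1 ratio under Reading A, or about 83% un-imaged under Reading B, and it is not a floor: at r = 0.1 the share is about 2%. These are also values the criterion permits, not values to be expected.
- **The rule is one-way.** It is meant for patients already selected for CT, and its sensitivity and NPV there are unaffected. A reader might infer that the plan promises 98% sensitivity for clinician and rule combined; it does not. It does claim to verify the sensitivity of clinical judgment, and that claim is at issue.
- **Relevant data are already planned.** All three category prevalences will be reported with intervals, and Global assessment of potential missed injuries adds a review of logs and records. The fault lies in the inference and in the choice of category 3 alone.
- **The sample size section does not mention sensitivity.** True; that link is made in Work-up bias assessment, and the 1.0% criterion serves it.
- **Dilution by trivial injuries.** A reader might infer that multiplying prevalence by the un-imaged count removes any such effect. That holds for the expected point estimate but not for exact limits: with 0 of 368 the upper limit stays at 0.997% however large the count. Nor can a lack of eligibility restrictions be held against a condensed article.

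**Conclusion.** The point holds in limited form. The 1.0% criterion bounds a predictive value, for one class of missed injury, and cannot by itself verify high sensitivity of imaging decisions. Depending on the assumed ratio, it is compatible with about 2% to 38% of injured patients going un-imaged (Reading A, ratios 0.1 to 3), or 5% to 15% (Reading B, un-imaged shares 25% to 75%). It agrees with the plan's 2% tolerance only at a ratio or share of about 0.1 or less. That the two quantities differ needs no assumption. The sizes rest on the assumed ratio, on how the 5% is read, and on treating major injury and the three-month outcome (procedure or death) as comparable, although their definitions differ.

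**What to change.** In Work-up bias assessment and the matching sample size section:

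1. Base the check of clinical judgment on all missed injuries, categories 2 and 3 together.
2. Report the implied clinician sensitivity with exact limits. Multiply the missed-injury prevalence and its limits by the un-imaged blunt-trauma count, and combine with the major-injury count in the imaged cohort. State that the two outcome definitions differ.
3. Take the un-imaged count from the ED logs. Study sites and subjects already says "We will review ED logs and identify patients who are not enrolled"; this would extend that review to un-imaged patients.

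Alternatively, limit the conclusion to an occult-injury prevalence below 1.0% among un-imaged patients, and remove the claim that this verifies the sensitivity of clinical judgment.

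The cost is a small extension of the log review and a weaker conclusion. With 368 patients, zero misses, a ratio of 1 and 5% injured among imaged patients taken as known, the lower limit for sensitivity is 0.05/(0.05 + 0.00997), about 83%. Enrolment need not change, but this sample cannot support a 98% claim at that ratio.
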